### Clinical and functional outcomes

Symptoms of depression at 5 months post baseline assessment measured as the difference in mean score on the Patient Health Questionnaire-9 (PHQ-9) [21,22] between the two arms. Difference in mean PHQ-9 would likely constitute a primary outcome in a later larger definitive trial.

We will explore remission from depression caseness (0/1) between the two arms at 6 weeks post-baseline. Remission is defined as PHQ-9 [21,22] score fallen by at least a 5-points from baseline and is below 10.

Symptoms of anxiety 5 months post baseline assessment measured as the difference in mean score on the GAD-7 [23] between the two arms.

Alcohol use at 5 months post baseline assessment will be measured using the Alcohol Use Disorders Identification Test (AUDIT), a 10-question alcohol use screening tool developed by the World Health Organisation.

Education outcomes will be measured using school records for school attendance and academic attainment. School attendance will be collected from the class register and measured as the proportion of days attended of the school academic year. Academic attainment will be collected from the continuous assessment and report cards of the adolescents. Academic attainment is measured as a score 0 – 100 for each subject in the term that the participant is enrolled in the study. The total score for each subject is made up of 30% from class assignments and test scores, and 70% from the examination score. The average score will be calculated from the participant’s total subject scores divided by the number of subjects.

### Measures for feasibility of conducting a fully powered trial

Feasibility of conducting a fully powered trial will be assessed by the number and proportion of adolescents screened using the brief screening tool, proportion of adolescents who complete the full eligibility assessment, proportion of adolescents eligible, number of weeks to complete the intervention and proportion of participants who complete follow up assessments at 5 months post baseline.

### Resource use and cost of the Y-MIND psychological intervention

Two types of resource use and cost data will be collected for the economic evaluation; patient and programme level costing of both direct (healthcare cost) and indirect (productivity loss) cost. Both financial (actual money spent) and economic cost (e.g., donated items and volunteering time) will be assessed. All recurrent costs related to delivery of the intervention to each participant and the capital cost including the start-up cost of implementing Y-MIND from a provider perspective will be assessed. All costs related to research activities such as the cost of research staff and data collection will be excluded.

### Data collection procedures and measures

#### At baseline.

Participants complete all self-report measures, with a research assistant using REDCap at baseline and follow up assessments. Table 1 details the timing of all measures.

**Table 1 pone.0319462.t001:** Timing of measures.

	Baseline	Intervention sessions	6 weeks after baseline	End of final intervention session	5 month follow up	Within 4 weeks after 5 months follow up
Feasibility outcomes						
Feasibility of Intervention Measure (FIM) (intervention arm only) [20]				X		
Intervention Appropriateness Measure (IAM) (intervention arm only) [20]				X		
Acceptability of Intervention Measure (AIM) (intervention arm only) [20]				X		
Semi-structured interviews with adolescents (intervention arm only)						X
Focus group discussions with Guidance and Counselling Coordinators who delivered the intervention				X		
PROOF fidelity tool evaluation (intervention arm only)		X				
Fidelity of receipt of intervention		X				
Clinical, economic and other outcomes						
Demographics	X				X	
School attendance and academic attainment	X				X	
Patient Health Questionnaire-9 [21,22]	X	X	X		X	
Economic outcomes (Child and Adolescent Service Use Schedule, EQ-5D-5L [24], Resource use questionnaire, Productivity lost questionnaire	X	X	X	X	X	
Alcohol use disorders identification test [25]	X				X	
Generalised anxiety disorder [23]	X				X	
Treatment expectations	X					
Measures for feasibility of conducting a fully powered trial						
Screening log	X (completed at screening)					
Recruitment Log	X					
Follow up log					X	X
Intervention attendance log (intervention arm only)		X				
Records of any referrals to nurse or other health professional			X	X	X	X

### Trial oversight and Safety monitoring and reporting

A Trial Management Group (TMG) will oversee the running of the trial, consisting of PIs, statisticians, data manager, project and trial manager(s) and co-investigators. The TMG will meet twice a month.

To ensure safety and integrity of the research an independent data safety and monitoring board (DSMB) will be established. The data safety and monitoring board (DSMB) will be chaired by a professional with appropriate expertise in trials of psychological interventions. It will consist of four members with experience in conducting clinical intervention research for psychiatric disorders particularly for young people. The DSMB will report any concerns to the trial management group. There will be no planned interim analysis and no formal stopping rules for this pilot trial.

In the event a participant experiences serious physical or psychological harm, that led to death, a life-threatening state or condition, hospitalisation or prolonged hospitalisation, persistent or significant disability or incapacity, physical or sexual abuse, suicidal or homicidal behaviour, or a security or data breach, the event will be reported to the DSMB and all research ethics committees [26]. A medical professional internal to the study will be consulted on whether the event was related to the participants involvement in the study. The events will be reported regardless of whether they were related to the study.

### Sample size

The sample size for this pilot trial will be 60 participants across 6 schools (10 in each school). 60 participants are deemed feasible to recruit and would provide sufficient data on feasibility, acceptability, and appropriateness of the intervention. Estimates of the standard deviation of FIM (scored as a mean across the items in the FIM scale) from two unpublished studies are 0.34 and 0.59. 60 participants will allow us to estimate the mean FIM score to within a 95% confidence level of between approximately ±  0.09 and ±  0.15 using these two standard deviation estimates.

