### Study design and setting

The study is a parallel arm cluster randomised controlled pilot trial. The unit of randomization will be clusters comprising Senior High Schools (SHS). The sampling frame will consist of all SHS (12 in number) in the Kassena-Nankana Municipal (KNM) and the Kassena-Nankana West District (KNWD), in the Upper East Region of Ghana. The districts are characterised by Guinea Savannah vegetation, with subsistence agriculture being the mainstay of the people. English language is the language of instruction, with Kassem and Nankani being the predominant s spoken languages in the settings. The KNWD hosts the Navrongo Health Research Centre (NHRC) which operates a demographic surveillance system that monitors the demographic dynamics of the populations (over 160,000) of both the KNM and the KNWD and facilitates tracking of study participants in longitudinal studies (Oduro et al., 2012).

Six SHSs will be selected based on the most populous schools. The six schools will each be randomly allocated 2:1 to either the intervention condition or enhanced usual care (EUC).

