### Randomisation

The six schools will each be randomly allocated 2:1 by simple randomisation to either the intervention condition or enhanced usual care (EUC) before screening and recruitment.

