### Youth in mind (Y-MIND) intervention

All participants in the intervention arm will receive the EUC (described above) plus the Y-MIND intervention. The Y-MIND intervention will be delivered by trained and supervised Guidance and Counselling Coordinators (GCC) at schools in 6 sessions. The first session will focus on psychoeducation on depression through storytelling to normalise the participant’s experiences of depression. After the psychoeducation the structure of the treatment is described and goals for therapy are agreed. Sessions 2 and 3 focus on helping the participant see the connection between their behaviour, daily activities, and low mood and activity scheduling. The GCC and participant agree specific and achievable goals based on participant’s interests, values, and preferences to promote active participation in activities that promote positive emotions and improve overall well-being. Sessions 4 and 5 focus on problem solving therapy, adapted from the Zimbabwean Friendship Bench (FB) intervention [19]. In these sessions, the GCC helps the participant identify and define a specific problem to work on, and break down problems into smaller components. The GCCand participant collaboratively brainstorm multiple possible solutions to the problem. The participant and GCC evaluate the potential solutions and consider their advantages, disadvantages, and feasibility together. The participant is encouraged to carry out the selected solution(s). In session 6 (last session) the GCC reviews the participant’s understanding of depression, including its symptoms and potential triggers to help participants recognise warning signs of relapse. Together, the GCC and participant work to create a personalized relapse prevention plan.

The PHQ-9 scores collected by the GCC at the beginning of each session will be collected for supervision purposes. If the participant’s PHQ-9 score has not changed this will be discussed in more detail with the Guidance and Counselling Coordinators and he/she will be provided with additional support from the clinical psychologist during the weekly supervision meetings.

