### Outcomes

#### Primary outcomes.

Feasibility of the intervention, from the perspective of the adolescents, is defined as extent to which the Y-MIND intervention can be successfully delivered by Guidance and Counselling Coordinators to reduce symptoms of probable depression within senior high schools in Navrongo. Feasibility of the intervention will be measured using the ‘Feasibility of Intervention Measure’ (FIM) [20] with adolescents at the end of their last intervention session, (or at their 5 month follow up if the intervention session was not attended). The 4-item measure assesses the perceived degree to which interventions or programs are feasible and appropriate. The FIM is measured on a 5-point Likert scale ranging from completely disagree (scored as 1) to completely agree (scored as 5). Item scores are calculated as a mean score of the responses.

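### The precision stated for the primary outcome (mean adolescent FIM) is worked out on 60 participants, but only the roughly 40 in the intervention arm give a FIM score

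*Protocol article*

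**What the plan says.** The primary outcome is the adolescents' mean FIM score. It is taken "with adolescents at the end of their last intervention session, (or at their 5 month follow up if the intervention session was not attended" (Primary outcomes).

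The Sample size section sets the total: "The sample size for this pilot trial will be 60 participants across 6 schools (10 in each school"). It gives FIM standard deviations that "from two unpublished studies are 0.34 and 0.59", then states the precision: "60 participants will allow us to estimate the mean FIM score to within a 95% confidence level of between approximately" ±0.09 and ±0.15.

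Three other places decide who can contribute a FIM score:

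- Study design and setting: "The six schools will each be randomly allocated 2:1 to either the intervention condition or enhanced usual care (EUC"). The Randomisation section repeats the ratio.
- Youth in mind (Y-MIND) intervention: "All participants in the intervention arm will receive the EUC (described above) plus the Y-MIND intervention". The control arm receives enhanced usual care without Y-MIND.
- Table 1, in the data collection section, lists "Feasibility of Intervention Measure (FIM) (intervention arm only").

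The guidance and counselling coordinators also complete the FIM, but the article lists this separately among the secondary feasibility outcomes.

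**The concern.** The precision sentence takes the whole trial as its denominator, while the measure is collected in one arm. Control adolescents have no Y-MIND sessions to rate, and Table 1 does not ask them to. The number behind the stated half-widths is therefore larger than the number of scores the design can produce.

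This matters because the FIM is the only primary outcome and this sentence is the only quantitative support for the sample size. In a pilot, precision does the job that power does in a definitive trial. A reader would credit the trial with a tighter estimate of its main result than it can give.

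**Working it through.** **Inputs from the protocol article.** Total 60, six schools, 10 per school (Sample size). Allocation 2:1 by school (Study design and setting; Randomisation). SD of FIM 0.34 and 0.59 (Sample size). FIM in the intervention arm only (Table 1). No ICC for FIM and no allowance for loss is given.

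**Step 1: reproduce the stated figure.** Half-width = 1.96 × SD/√n with n = 60.

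- SD 0.34: 1.96 × 0.34/√60 = 0.086, stated as 0.09.
- SD 0.59: 1.96 × 0.59/√60 = 0.149, stated as 0.15.

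The t distribution on 59 degrees of freedom gives 0.088 and 0.152, which round the same way. The stated figures therefore use all 60 participants, with no clustering and no loss.

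**Step 2: count the adolescents who can give a FIM score.** Taking the 2 of 2:1 as the intervention arm, 6 × 2/3 = 4 schools, and 4 × 10 = 40 adolescents.

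**Step 3: recompute with n = 40, independent observations.**

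| SD | Stated (n = 60) | z, n = 40 | t on 39 df, n = 40 |
|---|---|---|---|
| 0.34 | ±0.09 | ±0.105 | ±0.109 |
| 0.59 | ±0.15 | ±0.183 | ±0.189 |

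Like for like, the widening is √(60/40) = 1.22, or about 22%.

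**Step 4: number needed for the stated figures.** (1.96 × 0.34/0.09)² = 54.8, so 55. (1.96 × 0.59/0.15)² = 59.4, so 60. About 40 are available.

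**Step 5: sensitivity, on assumptions that are not in the article.**

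- *Missing FIM scores (z):* 10% loss (n = 36) gives ±0.111 and ±0.193. 20% loss (n = 32) gives ±0.118 and ±0.204.
- *School clustering:* the design effect is 1 + (10 − 1) × ICC, and the half-width is multiplier × SD × √(design effect/40). With 4 schools, the multiplier may be 1.96 or t on 3 df (3.182), depending on the interval method.

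| Assumed ICC | Design effect | z: SD 0.34 / 0.59 | t on 3 df: SD 0.34 / 0.59 |
|---|---|---|---|
| 0.01 | 1.09 | ±0.110 / ±0.191 | ±0.179 / ±0.310 |
| 0.05 | 1.45 | ±0.127 / ±0.220 | ±0.206 / ±0.357 |
| 0.10 | 1.90 | ±0.145 / ±0.252 | ±0.236 / ±0.409 |

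At a given ICC the choice of multiplier changes the result more than moving the ICC from 0.01 to 0.10 does. A clustered figure therefore means little unless its multiplier is stated.

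**The case against.** **Could the count reach 60 some other way?** No. The 5-month fallback picks up intervention-arm adolescents who missed the last session; it does not bring in controls. The coordinators' FIM is a separate outcome from different respondents. If simple randomisation gave a split other than 4:2, sixty adolescents would still require all six schools in the intervention arm and no control arm. Reading 2:1 in the other direction leaves 20 adolescents and ±0.149 and ±0.259 (z), which is worse.

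**Does it matter in a pilot?** This objection has force. No hypothesis test, power claim or progression threshold rests on the half-width. The Sample size section also justifies 60 as a feasible number to recruit, so the precision statement is not the only rationale. The absolute change is small, about 0.02 to 0.04 on a 1 to 5 scale. At SD 0.34 the corrected ±0.105 even lies inside the quoted range of ±0.09 to ±0.15. With n = 40 and a t multiplier of 2.023, the half-width stays within ±0.15 for any SD up to 0.15 × √40/2.023 = 0.47. These points limit the severity. They do not make 60 the right denominator.

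**Could the statistical analysis plan settle it?** It can fix the interval method, but it cannot make a published statement based on 60 agree with a table that allows about 40.

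**A stronger reading on clustering.** A reader might infer that the plan will analyse the FIM mean as independent observations and so ignore school. The article does not say that. Analysis of feasibility outcomes promises only suitable 95% intervals, and its examples are for proportions and counts. Independence is visible only in the planning figure, and the interval method may properly be left to the analysis plan. The article gives no ICC for FIM, so any clustered half-width is an illustration and should not be read as the trial's precision.

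**Conclusion.** The stated precision of the primary outcome is wrong as written. For about 40 intervention-arm adolescents the half-widths are about ±0.11 at SD 0.34 and ±0.18 to ±0.19 at SD 0.59, against ±0.09 and ±0.15 stated. This rests on the 2:1 allocation giving 4 intervention schools, on 10 adolescents in each, on complete FIM data and on independence. It needs no assumption about ICC or loss; a positive ICC or missing scores would only widen the intervals.

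The severity is moderate. A reader might go further and conclude that the trial is too small or that its feasibility aim is compromised. The documents do not support that, because they tie no decision to this half-width and the pilot can still describe FIM usefully with about 40 respondents.

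**What to change.** In the Sample size section, or in the analysis plan and results paper since the Trial status section reports that recruitment has ended:

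1. Restate the precision for about 40 intervention-arm adolescents in 4 schools, as about ±0.11 (SD 0.34) to ±0.19 (SD 0.59), and say that this assumes independent responses and no missing FIM scores.
2. Add a sensitivity note, labelled as assumption, that school clustering would widen it. At an ICC of 0.05 the half-widths are about ±0.13 and ±0.22 with a normal multiplier, or about ±0.21 and ±0.36 with t on 3 degrees of freedom. Quote the version whose multiplier matches the interval method that will be used for FIM.

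The cost is one corrected sentence and one added note. No extra participants or data are needed. The stated precision becomes less favourable: modestly under independence, and more so if the interval is built on 4 school means.

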### Analysis

#### Statistical methods.

A comprehensive statistical analysis plan will be developed by the trial statisticians with support from the senior statistician, which will be agreed on with the Y-MIND trial management team, then agreed on with the trial’s oversight committees and signed off by the chair of the executive committee. Although this is a pilot trial with feasibility rather than between arm clinical effectiveness as the aim, analyses will be performed on an intention to treat basis where appropriate. Every effort will be made to reduce loss to follow up and to collect outcome data from participants who have withdrawn from the intervention should they give permission to do so. Trial flow data will be reported as outlined by the CONSORT statement for cluster randomised trials (Campbell et al., 2004).

### Analysis of feasibility outcomes

The feasibility outcomes will be summarised with appropriate summary statistics (e.g., means and standard deviations/medians and interquartile ranges for normally distributed/non-normally distributed continuous outcomes; frequencies and proportions for categorical outcomes). Where appropriate some feasibility outcomes will either be reported only for the intervention arm, and/or will be reported separately by arm, along with appropriate 95% confidence intervals (i.e., confidence intervals for proportions for percentages, Poisson confidence intervals for count outcomes).

### Clinical and functional outcomes

The clinical and functional/educational outcomes will be summarised for the entire trial population and by trial arm, at baseline and outcome time points, with appropriate summary statistics. Where it makes sense to do so, an estimate of the appropriate difference between the arms and its 95% confidence interval at the five-month outcome time point will be reported. For continuous variables like PHQ-9, AUDIT, GAD-7, and educational performance, the mean difference between the arms will be estimated using mixed effects linear regression, with the five-month measure of the variable as the dependent variable, and with a random intercept for cluster/school. Each model will include baseline measure of outcome score where appropriate, and a dummy variable for trial arm. Other outcomes will be analysed in a similar manner, using an appropriate model link function and distributional family. For example, the between arm odds ratio for the proportion of days of school attended will be estimated using mixed effects logistic regression with a random intercept for cluster/school. We will aim to calculate an intraclass correlation coefficient (ICC) for the school clusters from the PHQ-9 model results, which will be used in the sample size calculation for the larger definitive trial, and to provide estimates of the ICC in schools in Ghana for such an intervention to publish in the literature.

We will explore remission from depression caseness (0/1) across the two arms at 6 weeks post-baseline using logistic regression, with the model including a dummy variable for trial arm. The comparison between the two arms will be expressed as an odds ratio.

This pilot trial is designed to gather data on feasibility outcomes and to estimate statistical quantities necessary to design a future trial. This analysis is not specifically powered to detect differences between arms in the clinical and educational outcomes. Therefore, where estimates of arm differences are presented, they will be treated as exploratory and not used as the basis for inferential statements.

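### The only between-arm estimate planned from the 6-week PHQ-9 is a remission odds ratio from a model naming arm alone, which gives up precision the scheduled data could provide

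*Protocol article*

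**What the plan says.** In Table 1 of the Protocol article (under Data collection procedures and measures), the row beginning "Patient Health Questionnaire-9 [21,22" is marked at baseline, during intervention sessions, at 6 weeks and at 5 months. The questionnaire itself, not just a remission status, is therefore collected at 6 weeks.

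Under Outcomes, Clinical and functional outcomes, the 6-week endpoint is a cut of that score: "Remission is defined as PHQ-9 [21,22] score fallen by at least a 5-points from baseline and is below 10".

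Under Analysis, Clinical and functional outcomes, the two time points are handled differently:

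- **Five months.** The plan says that "an estimate of the appropriate difference between the arms and its 95% confidence interval at the five-month outcome time point will be reported". Continuous outcomes, PHQ-9 among them, get a mixed linear model "with the five-month measure of the variable as the dependent variable, and with a random intercept for cluster/school". On covariates: "Each model will include baseline measure of outcome score where appropriate, and a dummy variable for trial arm".
- **Six weeks.** The plan is: "We will explore remission from depression caseness (0/1) across the two arms at 6 weeks post-baseline using logistic regression". Arm is the one term that it then names: "with the model including a dummy variable for trial arm". The result: "The comparison between the two arms will be expressed as an odds ratio".

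No between-arm difference in the 6-week score is planned. The same section calls all arm differences exploratory and not a basis for inference.

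**The concern.** Reducing a score to yes or no before comparing arms loses information, and leaving out a correlated baseline loses more. The protocol does both at 6 weeks and neither at five months, without giving a reason for the difference. It also says that the difference in mean PHQ-9 would likely be a primary outcome of the definitive trial, so a remission odds ratio is not on the scale that matters most for what follows.

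A second gap sits in the same sentence. Schools are the unit of randomisation, yet the 6-week model names no school term. Read as written, its interval would be too narrow if outcomes cluster by school.

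At stake is the precision and scale of one exploratory comparison. No decision in this pilot is tied to it.

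**Working it through.** **Inputs from the protocol.** 60 participants, 10 in each of 6 schools; 2:1 allocation, taken as 4 v 2 schools, hence 40 v 20 students; entry at PHQ-9 of 10 or more; remission as defined above. No precision or power figure is stated for the 6-week comparison (the sample-size section concerns the Feasibility of Intervention Measure only), so there is no figure of the plan's own to reproduce.

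**Assumed, because the protocol gives none.** 6-week PHQ-9 with SD 5 and mean about 10 under enhanced usual care, limited to 0-27; baseline correlation 0.3 or 0.5; ICC 0 or 0.05; benefit of 2, 3 or 4 points.

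**Step 1: information kept by a cut.** For a normal score cut at c so that a proportion p lies on one side, the efficiency of the binary analysis relative to the score is φ(c)² / [p(1 − p)]. Against a baseline-adjusted score with correlation ρ, multiply by (1 − ρ²).

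| Remission rate p | v unadjusted score | v adjusted, ρ = 0.3 (× 0.91) | v adjusted, ρ = 0.5 (× 0.75) |
|---|---|---|---|
| 20% | 0.49 | 0.45 | 0.37 |
| 30% | 0.58 | 0.52 | 0.43 |
| 40% | 0.62 | 0.57 | 0.47 |
| 50% | 0.64 | 0.58 | 0.48 |

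This treats remission as one fixed cut, so it is a guide only. Step 2 uses the protocol's two-part definition.

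**Step 2: power by simulation.** With ICC 0, the arm-only remission log odds ratio is compared with analysis of covariance on the score. Both had size of about 4-6% at zero effect.

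| Benefit | Remission | Baseline-adjusted score | Difference |
|---|---|---|---|
| 2 points | 21-24% | 31-37% | about 10-13 points |
| 3 points | 45-49% | 60-69% | about 15-20 points |
| 4 points | 68-72% | 84-90% | about 16-18 points |

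With ICC 0.05, individual-level tests were inflated (size 7-11%), so the fair contrast uses school-level t tests on 4 degrees of freedom (size about 5%). The gain from the adjusted score is then about 3-4, 7-8 and 9-13 percentage points for benefits of 2, 3 and 4 points.

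**Step 3: width of the planned estimate.** Take remission of 58% v 34%, that is 23.2 of 40 v 6.8 of 20:

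- Odds ratio = (23.2 × 13.2) / (16.8 × 6.8) = 2.68.
- SE of the log odds ratio = √(1/23.2 + 1/16.8 + 1/6.8 + 1/13.2) = 0.57.
- 95% interval = exp(0.986 ± 1.96 × 0.57), about 0.9 to 8, ignoring schools.
- With design effect 1 + 9 × 0.05 = 1.45, SE = 0.57 × √1.45 = 0.69, and the interval is about 0.7 to 10.

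**Step 4: the missing school term.** Design effects at ICC 0.02, 0.05 and 0.10 are 1 + 9 × ICC = 1.18, 1.45 and 1.90. The simulated false-positive rate of the arm-only logistic model at a nominal 5% was 6.4%, 8.8% and 11.3%.

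**The case against.** The strongest reply is that little depends on this comparison. The primary outcome is the Feasibility of Intervention Measure, the protocol disclaims power for clinical outcomes, and 6-week remission is only to be explored. Remission is also clinically interpretable in its own right. All of that stands and limits the weight of the point.

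The reply that an analysis plan not shown here will supply the detail is weaker. The protocol fixes the endpoint, time, model, term and effect measure for 6 weeks, separately from the five-month models. Its wording does not exclude further covariates, but it names none.

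Four stronger readings are tempting, and the document does not support them:

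- *The 6-week scores go unreported, so the time course cannot be seen.* The analysis section promises summaries by arm at baseline and at outcome time points. Six weeks is an outcome time point, so 6-week means by arm may well appear. What is absent is a modelled difference.
- *The pilot fails to produce what the definitive trial needs.* The five-month PHQ-9 is analysed as a score, with a random intercept for school, and the ICC is to come from that model.
- *The arm-only model is materially biased by baseline imbalance.* The bar does depend on baseline: a student starting at 10 must reach 5 or less, one starting at 14 or more must reach 9 or less. But students who start higher also tend to score higher at 6 weeks, which offsets this. Under assumptions like those above, the correlation of baseline with remission was only −0.04 to −0.23. At ρ = 0.5, remission rose from 0.39 to 0.44 (or from 0.44 to 0.52) between baselines of 10 and 14, though it fell at high baselines. A material bias is not shown.
- *Students lost after 6 weeks make this costly.* They would add nothing to a PHQ-9 mean difference, but no retention figure shows how many there would be.

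**Conclusion.** The point holds as a modest loss of precision in an exploratory comparison. At 6 weeks the plan estimates only a dichotomised effect, with neither baseline nor school named in the model, although the score is collected and a suitable model is already specified for five months.

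For this cluster design the relevant size is the ICC 0.05 result: about 3-13 percentage points of power for benefits of 2 to 4 points. The 10-20 point figure applies only without clustering and with individual-level tests, and should not be the headline. Both rest on an assumed SD, mean, correlation and effect. The direction of the loss held in every scenario tried; its size would change with other values. Power serves here only as a measure of precision, since the trial intends no inference from arm differences.

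**What to change.** In Analysis, Clinical and functional outcomes (or in the statistical analysis plan, before arm comparisons are run), add the between-arm difference in mean PHQ-9 at 6 weeks with its 95% confidence interval. Estimate it with the mixed linear model already specified for five months: baseline PHQ-9, arm and a random intercept for school. This supplies the baseline and school terms that the 6-week sentence does not name.

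Keep 6-week remission as a supportive exploratory outcome. If its odds ratio is reported with an interval, either allow for school there too or say plainly that the interval ignores clustering.

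A joint repeated-measures model for 6 weeks and 5 months, with arm-by-time terms, would let students seen only at 6 weeks contribute. It is optional.

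The cost is a sentence and one more model on data already scheduled, with no new participants, visits or measures. The downside is one more exploratory estimate to report.

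### The 6-week remission model names no school term although schools are randomised, so read plainly it would understate the uncertainty of the odds ratio

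*Protocol article*

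**What the plan says.** The design is clustered. Study design and setting states: "The unit of randomization will be clusters comprising Senior High Schools (SHS". Under Randomisation: "The six schools will each be randomly allocated 2:1 by simple randomisation". Sample size gives 60 participants in 6 schools, 10 per school. With the 2:1 ratio this means 4 intervention and 2 control schools, or about 40 against 20 adolescents.

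Remission is defined under Outcomes as a PHQ-9 "score fallen by at least a 5-points from baseline and is below 10", assessed at 6 weeks.

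The analysis section, Clinical and functional outcomes, specifies the between-arm models in two paragraphs:

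- The first covers the five-month comparisons. Continuous outcomes get a linear mixed model "with the five-month measure of the variable as the dependent variable, and with a random intercept for cluster/school". On covariates it says: "Each model will include baseline measure of outcome score where appropriate, and a dummy variable for trial arm". Other outcomes are to be handled along the same lines with a suitable link and family. The example is school attendance, analysed by a mixed logistic model with a school random intercept. A 95% confidence interval is promised for five-month arm differences.
- The second covers remission alone. It is to be explored "at 6 weeks post-baseline using logistic regression, with the model including a dummy variable for trial arm", and "The comparison between the two arms will be expressed as an odds ratio". The paragraph mentions no mixed model, random intercept or cluster-robust variance.

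The section closes by calling all arm differences exploratory and ruling out inferential use of them.

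**The concern.** When whole schools are allocated, adolescents in the same school tend to have correlated outcomes. The correlation inflates the variance of the arm comparison. Here the intervention is also delivered by each school's own Guidance and Counselling Coordinators, so differences between deliverers add to differences between schools. A logistic model without a school term assigns no variance to either source.

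The contrast with the paragraph before it makes the point more than an economy of wording. For attendance, also expressed as an odds ratio, the mixed model and the school intercept are written out. For remission they are not. If the text is followed literally, the remission odds ratio would be reported on a different footing from the PHQ-9 mean difference beside it, and it would look more precise than six schools allow.

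**Working it through.** **Plan's own figures.** The article gives no precision figure for remission and no ICC. Its only precision figure is for the mean Feasibility of Intervention Measure score. That figure reproduces without a clustering term: 1.96 × 0.34/√60 = 0.086 and 1.96 × 0.59/√60 = 0.149, matching the stated ±0.09 and ±0.15. It offers no ICC to borrow, so the ICC below is an assumption, shown over a range.

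**Inputs.** Cluster size m = 10 (Sample size). Schools 4 against 2 (six schools at 2:1, assuming that split is realised). All 10 per school are assumed to be assessed at 6 weeks. The ICC is assumed equal in both arms.

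**Formulas.** Design effect DE = 1 + (m − 1) × ICC = 1 + 9 × ICC. With equal school sizes it multiplies the variance in each arm alike, so the standard error of the log odds ratio should be √DE times the ordinary logistic one. Approximate true coverage of the nominal 95% interval is 2Φ(1.96/√DE) − 1. Effective sample size is 60/DE.

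| Assumed ICC | DE | SE factor √DE | Effective N | Coverage of nominal 95% interval |
|---|---|---|---|---|
| 0.01 | 1.09 | 1.04 | 55.0 | 94.0% |
| 0.02 | 1.18 | 1.09 | 50.8 | 92.9% |
| 0.05 | 1.45 | 1.20 | 41.4 | 89.6% |
| 0.10 | 1.90 | 1.38 | 31.6 | 84.5% |

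**Check by simulation.** 40,000 null trials were drawn for each ICC (beta-binomial, 4 against 2 schools of 10, remission assumed 40% in both arms). The ordinary logistic Wald test at the 5% level rejected in 5.0% of trials at ICC 0, and in 6.0%, 7.2%, 10.4% and 15.9% at the four ICCs above. These agree with the approximate coverages. A t-test on the six school proportions (4 df) stayed between 5.0% and 5.2% over the same range.

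**What it does to an interval.** Assume remission of 50% against 30%, purely as an illustration. The odds ratio is (0.5/0.5)/(0.3/0.7) = 2.33. The ordinary standard error is √[1/(40 × 0.5 × 0.5) + 1/(20 × 0.3 × 0.7)] = √(0.100 + 0.238) = 0.58, giving 0.75 to 7.29. Multiplying the standard error by √DE gives 0.59 to 9.20 at ICC 0.05 and 0.48 to 11.23 at ICC 0.10.

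**Few schools, kept separate.** With 6 − 2 = 4 df, the t multiplier is about 1.42 times 1.96. Combined with √DE, the interval would be 1.48, 1.54, 1.71 and 1.95 times as wide at the four ICCs. Only √DE is due to the missing school term. The rest applies equally to the article's random-intercept models, which specify no small-sample method either.

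**The case against.** The strongest reply is textual. The remission sentence says the model includes an arm dummy; it does not say that nothing else is included. The preceding paragraph extends its approach to other outcomes, and its logistic example has a school intercept. The full analysis plan, which the article says will be written, may settle the matter. This stands in part: a reader might infer that the authors chose a model with an arm term alone, and the text does not say so. But remission has its own specification, at a different time point, and the mixed-model wording used a few lines earlier is absent. At best the two paragraphs need reconciling.

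Three other replies succeed against stronger readings.

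- **A reported interval.** A reader might infer that the article commits to a 95% interval for remission that is too narrow. It promises intervals at five months, and for 6-week remission only an odds ratio. The point concerns any standard error or interval that the stated model would produce.
- **Baseline PHQ-9.** A reader might infer that omitting it is an error because remission is defined from baseline. Baseline enters the other models only where appropriate, and the attendance example names none. An unadjusted odds ratio is a legitimate randomised comparison, and adjustment changes the quantity estimated because odds ratios are non-collapsible.
- **Size and importance.** At an ICC of 0.01 to 0.02 the loss of coverage is small. The comparison is exploratory, the primary outcome is a feasibility score, and the ICC for the definitive trial comes from the PHQ-9 model. That limits the consequence, but it does not make the standard error right.

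**Conclusion.** The point holds in this form: the remission model as written names no allowance for the randomised unit, unlike the other models in the same section. For any positive ICC, the plain reading understates the uncertainty of the odds ratio. The standard error should be 1.04 to 1.38 times as large for ICCs of 0.01 to 0.10, and nominal 95% coverage would be about 94% down to 85%, before any few-cluster correction. These sizes rest on an assumed ICC, on 10 assessed adolescents per school and on a realised 4:2 split. The effect is small at the low end and material from about 0.05.

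Severity is moderate. No conclusion of the pilot and no stated design parameter for the later trial depends on this odds ratio. It is nevertheless a mismatch between analysis and design that can be removed at almost no cost.

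**What to change.** Amend the remission paragraph to say that remission at 6 weeks will be analysed allowing for school, by mixed effects logistic regression with a school random intercept, as for the other outcomes. Say also that the odds ratio will be reported with a 95% interval from a method suited to six schools. That can be a small-sample correction to the mixed model or a school-level comparison on 4 df. A school-level comparison of proportions yields a difference rather than an odds ratio, so if that route is taken the text should say which measure is reported.

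Adjustment for baseline PHQ-9, which is already collected, is optional. If it is used, it should be stated in advance.

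The cost is a sentence or two of wording and a few lines of code, with no new data. The one downside is a wider interval, which reflects what six schools can support.
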